#### **4.4 Number of Participants**

Seventy individuals will be invited to take part in this study.

Based on the results of the home-based sleep study, individuals with SRBD will be grouped into mild (minimum of 10), moderate (minimum of 10) and severe sleep apnea (minimum of 10).

Individuals without clinical warning signs for SRBD (minimum of 10) will undergo a home-based sleep study using ApneaLink™ in order to identify 10 study participants without SRBDs (“control cases”).

### **5.0 Selection of Subjects**

#### **5.1 Inclusion Criteria**

To take part in this study participant must:

- Have traumatic or nontraumatic (without risk for disease recurrence) cervical/thoracic (injury level at C1 to T6), complete/incomplete (AIS A, B, C or D) SCI who were not previously diagnosed and treated for sleep apnea.
- English-speaking adults 18 years of age or older
- At least 2 months after injury

Untreated sleep-related breathing disorders as an aggravating factor for neuropathic pain, cardiovascular dysfunction and spasticity following spinal cord injury

## **5.2 Exclusion criteria:**

- Patients with a non-traumatic spinal cord disease at risk for disease recurrence during the study (*e.g.*, demyelinating spine diseases such as neuromyelitis optica and multiple sclerosis, spinal cord malignancy); of note, patients with other causes of non-traumatic spinal cord disease are eligible for this study.
- Concomitant significant diseases of the central nervous system causing neurological deficits (*e.g.*, concomitant traumatic brain injury, stroke, dementia, Parkinsonism, multiple sclerosis)
- Preinjury chronic pain (*e.g.*, fibromyalgia)
- Psychiatric disorders that could affect the home-based sleep study using the ApneaLink™ and cardiovascular evaluations.
- Neuromuscular diseases (*e.g.*, myasthenia gravis)
- Current substance misuse
- History of primary hypersomnia (*e.g.*, narcolepsy, idiopathic hypersomnia). Of note, hypersomnia is defined as prolonged sleep periods (*i.e.*, more than 10 hours per night).

## **5.3 Withdrawal of Subjects**

### **(a) When and how to withdraw participants from the study intervention?**

The participant will be able to quit the trial at any moment if he/she withdraws consent, if his/her health status precludes a safe participation in the study.

The investigator may decide to terminate subject's participation in the study if he/she has not followed study procedures. This study may be stopped at any time by the investigators.

## **6. Assessment of Safety**

All adverse events will be recorded and used to assess participant safety.

### **6.1 Adverse Events Monitoring**

Adverse events (AE) will be collected continually throughout the study. The study clinician is responsible for reviewing and signing off on documentation of events meeting the criteria and definition of an AE or Reportable Event as provided in this protocol. All AEs and Reportable Events will be recorded. Adverse events will be entered in participant's charts and recorded on the appropriate case report form (CRF) page from the time written informed consent is obtained until completion of the study or until resolution of the reportable event.

Information to be collected includes the nature, date, time of onset, intensity, duration, causality, and outcome of the event. If an AE is assessed by the Investigator as not reasonably attributable to study intervention, its occurrence must also be recorded in the source documents and reported on the CRF.

### **6.2 Procedure for Serious Adverse Events**

In the case of a Serious Adverse Event (SAE) the site lead clinician or designee must immediately (within 1 working day/24 hours of learning of its occurrence) report the SAE by phone or email to

Untreated sleep-related breathing disorders as an aggravating factor for neuropathic pain, cardiovascular dysfunction and spasticity following spinal cord injury

the study project manager. The signed and dated serious adverse event form must be emailed on the provided CRF to the study project manager within 48 hours of the site's knowledge of the SAE. The site lead clinician must attach a photocopy of all examinations carried out and the dates on which these examinations were performed. Care should be taken to ensure that the participant's identity is protected on all copies of source documents provided to the project manager.

A follow-up on any SAE that is fatal or life threatening should be provided within 5 calendar days. The study clinician is accountable to ensure safety of the participants, including referral to a specialist if indicated. Notably, the study clinician must follow up on the outcome of any adverse events (clinical signs, laboratory values or other, etc.) until they return to normal, or stabilization of the participant's condition. This implies that follow-up may continue after the participant has completed the study.

## **7. Statistics**

The baseline characteristics and outcomes measures among the four study groups will be analyzed using the Kruskal-Wallis test (non-parametric data) or ANOVA (parametric data). Study groups will also be compared using Fisher exact test regarding categorical variables. The costs of the home-based sleep study will be compared to the costs of the polysomnography using Mann-Whitney U test. Sample size and feasibility: Using pain (VAS) as the primary outcome measure, an estimated sample size of 10 subjects per group is required to detect a "minimal clinically important difference" of at least 25 mm in the VAS with a minimum power of 90% and a significance of 5% for 2-sided comparison tests.

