### ***Sleep disorders after SCI***

A variety of sleep disorders have been described in individuals with SCI including insomnia and sleep-related breathing disorders (SRBDs). In a review of 11 epidemiological studies, the mean prevalence of SRBDs was 6% in men and 4% in women in the general population. In comparison, SRBDs have been reported in 48% to 91% of individuals with tetraplegia, and 13% to 63% of individuals with paraplegia. Although the frequency of SRBDs after SCI is much greater than in the able-bodied population, this is still a largely under-studied secondary condition in the SCI population.

Untreated sleep-related breathing disorders as an aggravating factor for neuropathic pain, cardiovascular dysfunction and spasticity following spinal cord injury

In a recent qualitative study, 20 individuals with SCI voiced several barriers to good quality sleep including SCI-related dysfunction, care, sleep environment, pain, anxiety, and avoidance. In summary, “sleep problems, such as those described by participants in this study, have the potential to exacerbate several conditions that commonly occur after SCI and to significantly affect health-related quality of life.”

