#### **4.1.1 Primary Outcome measures:**

- a) The presence and intensity of neuropathic pain as assessed using the Visual Analog Scale (VAS; range: 0 to 100) and daily amount of analgesics (pregabalin, neurontin, opioids, etc.);

Untreated sleep-related breathing disorders as an aggravating factor for neuropathic pain, cardiovascular dysfunction and spasticity following spinal cord injury

- b) The cardiovascular activity during sleep based on the peripheral arterial tone and overall heart rate variability as recorded using the Bittium Faros™ 180 device and Caretaker™ Medical cNIBP monitor device;
- c) The number of episodes of autonomic dysreflexia during sleep and their association with apneas and hypopneas by combining the recorded data from the ApneaLink™, Bittium Faros™ 180 device and Caretaker™ Medical cNIBP monitor devices;
- d) The degree of spasticity in the upper and lower limbs as assessed using the Modified Ashworth Scale;
- e) Serum CRP level.

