- (d) At discretion and expenses of the research assistant and [name] (co-investigator at Sunnybrook Health Science Centre, the home-based sleep study devices can be either send by especial and secure courier (e.g. FEDEX) or picked up by the research assistant at the study participant's residence on next the day after the test. The study participant must agree with the latter option before the research assistant can drop by their residence. All the costs for either option are included in the price for the service as per the revised inter-institutional agreement.
- (e) The research assistant must properly destroy all PHI right after completing of the home-based sleep studies. The only information that should be maintained includes the study participant ID number and data on how many times and the reasons for phone calls and/or visit to provide technical support.

(2) Individuals living with SCI are often on pharmacologic treatment for neuropathic pain and/or spasticity. Given their potential confounding effect, we will collect information on the medicaments taken at the time of the studies in order to properly analyze the results of both studies.

(3) All the laboratory blood tests will be carried out by a company that provides high-quality services using standardized assays and methods across Canada. This will facilitate the comparisons and interpretation of the results from this research project.

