## **11. Data Handling and Record Keeping**

Participant data will be collected on Case Report Forms (CRFs). Prior to the start of the study, the PI will complete a Delegation of Authority Form showing the signatures and handwritten initials of all individuals who are authorized to perform study tasks, specifically those who have

Untreated sleep-related breathing disorders as an aggravating factor for neuropathic pain, cardiovascular dysfunction and spasticity following spinal cord injury

been authorized to make or change entries in CRFs. The PI or designee will provide completed CRFs for each participant. All required data are to be recorded in the CRFs. Completed CRFs will be reviewed by the PI or designee to ensure completeness and consistency. An explanation must be documented for any missing data.

Collected data will be stored at hospital network drive. This drive will be backed up on regular basis and will be protected using a firewall. In the event the firewall is not functioning, the hard drives with the participants' data have to be disconnected from Local Area Network (LAN) or Wide Area Network (WAN).

Collected data will be available for statistical analysis according to the methods described in Section 7 Statistics. After the study is completed and the results are published, data will be stored for ten years. After ten years, the data will be destroyed. In the event of inappropriate release of personal health information the following will be done: further release of information will be stopped, any information that can be retrieved, the UHN Privacy Office and REB will be notified, and then further actions may be taken according to recommendations from the UHN Privacy Office and REB.

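### Section 7 compares non-randomised SRBD groups only with unadjusted tests, so a group difference can reflect injury level or medication rather than SRBD

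*Protocol*

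**What the plan says.** Section 7 gives the outcome analysis in two sentences: "The baseline characteristics and outcomes measures among the four study groups will be analyzed using the Kruskal-Wallis test (non-parametric data) or ANOVA (parametric data") and "Study groups will also be compared using Fisher exact test regarding categorical variables". The only other test named is a Mann-Whitney test for costs. No covariate, stratum, matching rule or regression model appears. Section 11 makes this list the operative one: "Collected data will be available for statistical analysis according to the methods described in Section 7 Statistics".

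The four groups (no SRBD, mild, moderate, severe) are formed from the home sleep test (sections 4.3 and 4.4).

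Three other places bear on the comparison:

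- **Injury level and SRBD.** Section 2.1 says "SRBDs have been reported in 48% to 91% of individuals with tetraplegia, and 13% to 63% of individuals with paraplegia".
- **Who is enrolled.** Section 5.1 admits "cervical/thoracic (injury level at C1 to T6), complete/incomplete (AIS A, B, C or D) SCI", so tetraplegia and paraplegia share one cohort. No rule balances them across groups.
- **Medication.** Section 4.2, item (2), on drugs for neuropathic pain and spasticity, says "Given their potential confounding effect, we will collect information on the medicaments taken at the time of the studies"; the stated purpose is a proper analysis. Section 4.1.1(a) also makes "daily amount of analgesics (pregabalin, neurontin, opioids, etc".) part of the primary pain outcome, beside the VAS.

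**The concern.** All three primary objectives in section 3.1 concern an association with SRBD. In an observational comparison, a factor that is linked to SRBD and also affects the outcome produces a group difference even if SRBD does nothing.

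The protocol supplies one such factor, injury level, and names another, medication. It then fixes tests that can use neither. Comparing baseline characteristics between groups can show an imbalance but does not correct it.

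Medication raises two further problems. A pain score lowered by analgesics can hide a real association. Analgesic amount is also both a component of the primary outcome and a named confounder, with no rule for how it enters the analysis.

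The results are meant to inform a later CPAP trial (section 2.2), so a spurious or masked association would carry forward.

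**Working it through.** The plan gives no figure for confounding, so there is nothing of its own to reproduce. The check asks how far the planned tests could be misled by injury level alone.

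**Inputs from the protocol**
- SRBD prevalence: 48-91% in tetraplegia, midpoint (48+91)/2 = 69.5%; 13-63% in paraplegia, midpoint (13+63)/2 = 38%.
- Group size: 10 per group (section 7). Seventy invited over four groups gives 70/4 = 17.5, taken as 17.
- Tests: Kruskal-Wallis or one-way ANOVA on four groups, two-sided 5%.

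**Assumptions, not in the protocol**
- A 50:50 cervical/thoracic mix.
- Paraplegia prevalences apply to T1-T6.
- The same tetraplegia share in the mild, moderate and severe groups.
- Level shifts a normally distributed outcome by 0.5 or 1 SD.
- SRBD has no effect.

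**Step 1: imbalance in level.** With pT and pP the prevalences in tetraplegia and paraplegia, and equal numbers of each:

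- share tetraplegic among SRBD = pT/(pT + pP) = 0.695/(0.695 + 0.38) = 0.647
- share tetraplegic among controls = (1-pT)/[(1-pT) + (1-pP)] = 0.305/(0.305 + 0.62) = 0.330
- difference = 0.317, or 32 points

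| Prevalences used (tetraplegia v paraplegia) | SRBD | Control | Difference |
|---|---|---|---|
| Midpoints, 69.5% v 38% | 65% | 33% | 32 points |
| Both low ends, 48% v 13% | 79% | 37% | 41 points |
| Both high ends, 91% v 63% | 59% | 20% | 40 points |
| Widest, 91% v 13% | 88% | 9% | 78 points |
| Ranges crossed, 48% v 63% | 43% | 58% | -15 points |

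At midpoints, a mix of 30:70 or 70:30 still gives 27-28 points.

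**Step 2: spurious difference.** This is the imbalance times the level effect. At midpoints it is 0.317 × 1 SD = 0.32 SD, or 0.317 × 0.5 SD = 0.16 SD. It does not shrink as the sample grows.

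**Step 3: false-positive rate of the planned tests**, by simulation (Kruskal-Wallis and ANOVA, nominal 5%):

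| Scenario | 10 per group | 17 per group |
|---|---|---|
| Midpoints, 1 SD level effect | about 9% | 11-12% |
| Matched ends, 1 SD | 10-11% | 15-17% |
| Widest, 1 SD | 32-33% | 55-57% |
| Midpoints, 0.5 SD | 5-7% (both sizes) | |

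With the ranges crossed the rate stays near nominal, at 6-7% or less. An ANOVA with injury level as covariate gave about 5% in every scenario.

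**Step 4: medication.** The protocol has no figures for drug use by group, so no size can be computed. The defect shows when the sections are set side by side. Section 4.2 promises to record drugs so that the results can be analysed properly, section 11 sends the analysis to section 7, and no section 7 method can use the drug data.

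**The case against.** The best defence is that covariates and models are commonly left to a statistical analysis plan, which is not shown, and that section 4.2 does recognise medication. That covers an unwritten covariate list. It does not cover a protocol that names specific unadjusted tests for the primary outcomes and states that the data will be analysed by those methods. For medication the fair description is an intention with no method; a reader might infer that medication is ignored, and the text does not support that.

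Other points on that side do stand and limit the claim:

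- A reader might infer that injury level drives SRBD and that level differences will be reported as an SRBD effect. The protocol reports an association, with overlapping ranges, and the imbalance reverses if the ranges cross. Only that a difference can reflect level is supported.
- The prevalences cover paraplegia in general. No figure is given for T1-T6, and limiting enrolment to C1-T6 may itself narrow the contrast.
- No passage quantifies an effect of level on pain, the outcome used for the sample size. Section 2.2 links interrupted descending pathways to autonomic dysfunction, so the concern is most plausible for the cardiovascular outcomes. For spasticity, section 2.1 gives a frequency in tetraplegia only, with no comparator.
- Larger error rates can be had by pooling all SRBD participants against controls in a Mann-Whitney test. Section 7 plans that test for costs only, so those rates do not describe this plan.

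**Conclusion.** The point holds in a limited form. Section 7 commits the primary associations to unadjusted tests although the protocol itself reports SRBD differing by injury level and names medication as a potential confounder. Followed as written, the plan cannot separate an SRBD effect from either.

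For injury level the likely inflation is modest: from 5% to roughly 9-12% at mid-range prevalences with a 1 SD level effect, and close to nominal with 0.5 SD. The rates above 30% need the widest prevalence contrast and should not be taken as expected. All of these rest on the assumed mix, level effect and use of general paraplegia prevalences. A reader might infer that a biased pain result has been demonstrated; it has not, because the documents give no level effect on the VAS. The case for changing the plan is that the bias persists at any sample size and can be reduced with data already being collected.

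**What to change.** Rewrite section 7 so that the primary analysis of each outcome is an adjusted comparison of the SRBD groups, by ANCOVA or a rank-based or ordinal equivalent:

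- **All outcomes:** injury level (cervical v thoracic) as covariate, with AIS completeness added if numbers allow.
- **Spasticity:** add antispastic drug use.
- **Pain:** report analgesic amount as an outcome in its own right, and adjust the VAS for it only in a sensitivity analysis. It is part of outcome (a) and may lie on the causal path, so it should not enter the main pain model.
- **Unadjusted tests:** keep Kruskal-Wallis, ANOVA and Fisher as descriptive.

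Keep the list this short. Five or six covariates plus three group terms would be eight or nine parameters for 40 to 70 participants, which is too many, and the simulation held 5% with level alone.

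The cost is one to three degrees of freedom and slightly less precision. No new data are needed: injury history is in Table 1 and medication is recorded under section 4.2. Confounding by unmeasured factors would remain and should be stated as a limitation.

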### **3.2 Secondary study objectives:**

- (1) To confirm that a home-based sleep study is a feasible alternative for diagnosis of SRBDs in tetraplegics and paraplegics;
- (2) To compare the costs of a home-based sleep study with the conventional polysomnography in an overnight sleep clinic using cost-minimization analysis.

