#### **4.2 Description of the type/design of the study**

This is 3-year cross-sectional, prospective study.

- (1) Individuals with SCI frequently decline to stay overnight to complete formal polysomnography due to their concerns about availability of proper support, funding for attendants and the accessibility of the sleep disorder clinics. Given this, we decided to use a home-based or hospital-unattended sleep test (ResMed ApneaLink Air™) that is a practical, less costly, validated and reliable surrogate for diagnosis of the SRBDs. A trained research assistant from Sunnybrook Health Science Centre with expertise on the setting up and use of ResMed ApneaLink™, Bittium Faros™ 180 and Caretaker™ Medical cNIBP monitor devices will be available to assist the participants who have questions or problems with setting up the sleep apnea testing. The process for the technical support for the home based-sleep study will include the following steps:
  - (a) The research assistant from Sunnybrook Health Science Centre will receive a notification by phone from the research coordinator from Lyndhurst stating that a new participant will undergo home-based sleep studies. The study participant identifying number (i.e. “study participant ID #...”) along with their address and minimal clinical information (only level and severity of spinal cord injury) will be provided.
  - (b) The study participant will receive the name and phone number of the research assistant from Sunnybrook Health Science Centre and will be instructed to call them if there are any questions or concerns only during home-based sleep study (12 hours overnight support).
  - (c) If the study participant is unable to set up the home-based sleep study devices, they will be offered to receive a visit from the research assistant at their residence. If the study participant agrees, the research assistant will provide technical support at their residence.

Untreated sleep-related breathing disorders as an aggravating factor for neuropathic pain, cardiovascular dysfunction and spasticity following spinal cord injury

If the study participant disagrees and the setting up is not possible, the study participant will be withdrawn from the study.

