Those individuals with clinical warning signs for SRBDs will undergo a home-based sleep study using the ApneaLink™ (Picture 1) device to confirm the diagnosis of SRBD (n=30). Based on the results of the home-based sleep study, individuals with SRBD will be grouped into mild (n=10), moderate (n=10) and severe sleep apnea (n=10). Also, individuals without clinical warning signs for SRBD will undergo a home-based sleep study using ApneaLink™ in order to identify 10 study participants without SRBDs (“control cases”).

All participants will also undergo cardiovascular evaluation during sleep using the Bittium Faros™ 180 (Picture 3) and Caretaker™ Medical cNIBP monitor (Picture 2) devices to assess sympathetic activity during sleep in all study participants (n=40). All participants will be examined with regards to their degree of spasticity as assessed using the Modified Ashworth Scale. Also, all participants will undergo laboratory blood tests to measure their serum CRP level.

Furthermore, an economic analysis will be undertaken in order to compare the costs of the home-based sleep study with the conventional polysomnography in a sleep clinic. For this purpose, the costs of the home-based sleep test will be estimated based on our experience during this study. The costs of the conventional polysomnography will be obtained from the sleep clinic at Sunnybrook Hospital where [name], co-investigator in this study, works. The professional and technical fees will be derived from the Ontario Health Insurance Plan (OHIP) – Schedule of Benefits, Physician Services.

All participants who are diagnosed with moderate-to-severe SRBDs during the study will be referred to [name] or other sleep specialist for consultation and CPAP therapy. Also, study participants whose CRP levels are greater than 10 mg/L (normal range up to 3 mg/L) will be immediately referred to their family physician (or emergency if symptoms or signs of systemic infection) for further investigations and treatment because a CRP greater than 10 mg/L is suggestive of infection or primary inflammatory disease.

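### The Mann-Whitney cost comparison has no defined polysomnography sample, and a rank test does not estimate the saving that the cost-minimization objective asks for

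*Protocol*

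**What the plan says.** Section 3.2 of the protocol sets as secondary objective 2 a comparison of the cost of a home sleep study with that of conventional polysomnography, "using cost-minimization analysis". Section 4.1.2 lists the matching economic outcome. Section 7 names the test: "The costs of the home-based sleep study will be compared to the costs of the polysomnography using Mann-Whitney U test".

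The inputs are described elsewhere:

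- **Polysomnography (section 4.3):** "The costs of the conventional polysomnography will be obtained from the sleep clinic at Sunnybrook Hospital".
- **Fees (section 4.3):** "The professional and technical fees will be derived from the Ontario Health Insurance Plan (OHIP) – Schedule of Benefits, Physician Services".
- **Home test (section 4.3):** "the costs of the home-based sleep test will be estimated based on our experience during this study".
- **Return of the devices, by courier or pick-up (section 4.2, item 1(d)):** "All the costs for either option are included in the price for the service as per the revised inter-institutional agreement".

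Table 1 in section 4.3 lists the home devices and no polysomnography. Section 4.2 explains that an unattended test was chosen because people with spinal cord injury often decline an overnight stay in a sleep clinic.

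**The concern.** A Mann-Whitney U test compares two sets of independent observations. The home-test side can supply one cost per participant. For the polysomnography side the protocol gives no unit of observation, no source of individual costs and no number of values. If the clinic supplies a price, the analyst has to decide how often to enter it, and nothing in the protocol settles that. The choice can move the result across 5%.

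There is also a mismatch with the objective. A cost-minimization analysis asks how much one option saves. A rank test addresses whether costs in one set tend to be lower and gives no amount. Section 2.2 expects administrators and policymakers to use the result when deciding whether to offer unattended sleep studies, and they need the amount.

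**Working it through.** **The plan's own figure.** There is none to reproduce. The only sample-size statement in section 7 (10 per group) concerns VAS pain. No number, effect size or power is given for the cost comparison.

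**Inputs.**
- Home tests: n = 40 (number of study participants in section 4.3) or n = 70 (number invited in section 4.4).
- Polysomnography entries: m, not given in the protocol. Assumed values are 1, 2, 10 and 40.
- Polysomnography cost: assumed to be one price, entered m times.
- Share of home costs below that price: not given. Varied from 50% to 100%.

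**Formula.** Asymptotic two-sided test with continuity and tie correction, where N = n + m and t is the size of each group of tied values:

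z = (|U − nm/2| − 0.5) / √V, with V = (nm/12) × [(N + 1) − Σ(t³ − t)/(N(N − 1))].

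**Worked cases: n = 40, every home cost below the price, home costs untied** (so |U − nm/2| = nm/2).
- m = 1: nm/2 = 20; V = (40/12) × 42 = 140; z = 19.5/11.83 = 1.65; p = 0.099.
- m = 2: nm/2 = 40; V = (80/12) × [43 − 6/(42 × 41)] = 286.6; z = 39.5/16.93 = 2.33; p = 0.020.
- m = 40: nm/2 = 800; V = (1600/12) × [81 − 63960/(80 × 79)] = 9451; z = 799.5/97.2 = 8.22; p = 2e-16.

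**Across assumptions (asymptotic p).**

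| n | Home costs below the price | m = 1 | m = 2 | m = 10 | m = 40 |
|---|---|---|---|---|---|
| 40 | 100% | 0.099 | 0.020 | 1.2e-06 | 2e-16 |
| 40 | 80% | 0.33 | 0.17 | 0.0036 | 8e-07 |
| 40 | 70% | 0.53 | 0.36 | 0.053 | 0.0010 |
| 40 | 60% | 0.77 | 0.66 | 0.34 | 0.10 |
| 40 | 50% | 1.0 | 1.0 | 1.0 | 1.0 |
| 70 | 70% | 0.51 | 0.35 | 0.042 | 0.0004 |

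Within a row the home data are identical and only the number of repeated entries changes. At 70% below with n = 40, the same data run from p = 0.53 to p = 0.001. The 50% row does not move. So p depends on n and on the share below the price as well as on m. It is with the first two held fixed that the arbitrary m decides the result.

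**Exact or asymptotic.** With one polysomnography entry and untied home costs, the smallest exact two-sided p is 2/(n + 1). For n = 40 this is 2/41 = 0.049, against 0.099 from the asymptotic test on the same data. With m = 1, the choice of calculation alone crosses 5%.

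**If the home cost is also one price.** With n = 40 and m = 1 all 40 home values are tied, V = (40/12) × [42 − 63960/(41 × 40)] = 10, z = 19.5/3.16 = 6.17 and p = 7e-10. This is an artefact of the ties, since only two distinct numbers are being compared.

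**Size of the saving.** With n = 40 and all home costs below the price, a gap of 1, 10, 100 or 500 cost units gives the same p at each m. That is true of any rank test under complete separation. It is not itself evidence of the missing sample, but it shows that the test cannot supply the amount saved.

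**The case against.** The best defence is that the protocol never says the polysomnography cost is a single price. Section 4.3 speaks of costs obtained from the clinic, and the clinic could supply costs for individual patients. The fee-schedule sentence covers professional and technical fees only and may apply to both tests. Costing detail can also be left to an analysis plan that is not shown, and the Mann-Whitney sentence need not be the whole of the economic analysis.

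Part of this stands. Individual clinic costs are not excluded, so a reader who infers that the polysomnography cost is certainly a constant goes further than the text. But the protocol describes no such sample, and it does not leave the method open: section 7 names a two-sample test, and it is the only statistical method given for the costs. Even with a genuine second sample, that test would not estimate the saving.

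Two other strong readings are tempting and are not supported:

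- **That the p-value depends only on the number of entries.** It also depends on the number of home tests and on the share of them below the price. At a 50% share it is 1.0 whatever the number of entries.
- **That the home-test cost is largely a contract price.** The sentence in section 4.2, item 1(d), concerns the two ways of returning the devices. The protocol does not say what share of the total this is, and section 4.3 bases home costs on study experience.

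**Conclusion.** Wrong as written, with moderate severity. The protocol commits to a two-sample test without defining the second sample, and the test does not answer the cost-minimization objective. Both statements follow from the text without further assumption.

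The size of the effect on the p-value is conditional. It assumes that the polysomnography cost is a clinic price plus schedule fees. On that reading, with 40 home tests all below the price, p is 0.099, 0.020 or about 2e-16 for one, two or forty entries. With 70% below, it is 0.53, 0.36 or 0.001. Such a p-value has no inferential meaning.

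The point touches secondary objective 2 only. The primary outcomes, the comparisons among the four groups and the sample size are unaffected.

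**What to change.** Delete the Mann-Whitney sentence from section 7 and replace it with the following:

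- Report the mean home-test cost per participant over all attempted tests. Include set-ups that fail and lead to withdrawal under section 4.2, item 1(c), because their costs would otherwise drop out in favour of the home test.
- Give a 95% confidence interval where costs vary by participant.
- Subtract the polysomnography cost as a fixed reference value, state its components and sources, and give a sensitivity range on that value.

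If the sponsor does intend to collect individual polysomnography costs from the clinic, section 7 should define that sample (unit, source and number) and compare mean costs.

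The price is an uninterpretable p-value and a little more costing work. Section 4.2, item 1(e), already keeps the number of support calls and visits and the reasons for them. The costs of failed attempts would have to be recorded as well.
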